## Abstract

**Background:**

Understanding the factors influencing food choice is critical for developing effective strategies to promote healthier eating habits and creating policies that support public health. Attentional bias, the inclination to focus attention on specific stimuli, plays a significant role in shaping food preferences by affecting how individuals perceive and react to various food-related elements. Various methodologies exist to examine attentional bias, including the dot-probe task, which measures reaction times to probes appearing after paired stimuli (eg, novel vs familiar food images); eye-tracking, which tracks gaze patterns and fixations to determine visual attention; and electroencephalography, which records brain activity, capturing early and late neural responses (eg, N100, P300) linked to attention processing; however, integrated approaches combining these methods to assess bias toward familiar versus novel foods remain underexplored.

**Objective:**

This study aims to examine differences in attention toward familiar versus novel food stimuli using integrated eye-tracking, dot-probe, and electroencephalography methods, and to explore associations with self-reported food choice.

**Methods:**

A total of 40 healthy adult participants will be recruited. Participants will be presented with pairs of familiar or novel food images, while their visual attention and brain activity are recorded concurrently. Eye-tracking metrics, including time to first fixation and total fixation duration, will be used to assess visual attention. Electroencephalography data will be collected to measure the amplitude of event-related potential components, such as P300 and N100, associated with attentional processing. Reaction times will also be recorded as a behavioral measure of attentional engagement with familiar versus novel food items. Data analysis will involve repeated measures ANOVA to examine the effects of food familiarity and novelty on attentional bias metrics. Correlation analyses will also be conducted to explore the relationships between eye-tracking, electroencephalography, and dot-probe measures.

**Results:**

This study was approved by the Ethics Committee of the Iran University of Medical Sciences in February 2021 and funded in January 2022. Data collection began in November 2022 and is expected to be completed in July 2025. As of the submission of this study, 36 individuals have been recruited. Data analysis has not yet commenced, but it is planned to begin upon the completion of data collection. The results are anticipated to be published by December 2025. The protocol was registered with the Open Science Framework in September 2024.

**Conclusions:**

The main outcome of this study is identifying differences in attentional bias metrics toward familiar versus novel food stimuli at different presentation times. These findings will provide preliminary data on the application of an integrated approach for capturing attentional bias to food-based stimuli based on their familiarity or novelty, and how these biases may be linked to food choice behaviors.

**International Registered Report Identifier (IRRID):**

DERR1-10.2196/69541

## Introduction

Food decision, including choices around types, timing, and portions, is a response shaped by various stimuli and directly influences both energy and nutrient intake [1,2]. Food choices are influenced by individual preferences and postconsumption reactions to food intake. The attention individuals give to food depends on the stimuli that automatically act on them (bottom-up factors) and is also determined by their interests and goals (top-down factors) [3,4]. Bottom-up and top-down processing occur simultaneously and interact with each other [5]. Bottom-up factors act automatically on the consumer and include certain characteristics for processing basic stimuli such as size, color, or shape [6]. Top-down factors are related to the person themselves [7]. They include the consumer’s voluntary search for and attention to specific food product information [8], as well as the processing of individual experiences, motivations, and expectations. In research on the impact of information provision on food choices, it is often assumed that individuals attend to all provided information. However, individuals may not notice or perceive all the information presented [9]. If information is unattended to, it cannot inform choice [10]. Thus, it is important to evaluate if and how people pay attention to information, and the factors influencing such attention or inattention.

Visual attention is an important factor in the food decision-making process, providing a key contribution to subsequent decision-making [7]. Understanding attentional bias, where individuals preferentially process specific types of information, has been critical in understanding food-related behaviors in the context of consumer behavior or etiology of diseases, namely obesity [11]. Attentional bias has been measured using novel psychophysiological methods, including eye-tracking [12]. Eye-tracking technology provides an objective way to measure eye fixation duration and movement, capturing visual attention toward prominent stimuli [13,14]. In eye-tracking, participants are presented with pictures, either concurrently with reaction- and time-based paradigms or with instructions to simply gaze at pictures presented. One well-documented reaction time paradigm is the dot-probe task. In this task, participants are presented with cues of varying duration, which impacts the interpretation of attentional bias [15]. Previous research suggested stimulus presentation lengths of ≤200 milliseconds being associated with automatic orientation of attention, whereas presentation lengths ≥500 milliseconds are associated with maintained attention [16]. Currently, there are several studies in the literature applying either eye tracking or dot-probe to investigate the attentional bias to different food or nonfood stimuli among the healthy population or across disorders, such as anxiety, obesity, and eating disorders [17-20]. While visual probe tasks are the most commonly implemented task assessing food-related attentional bias, some current evidence has called their test-retest reliability into question and suggests combining different methods of attentional bias assessment for obtaining more reliable results [21].

While some previous studies have suggested a role for visual attentional bias toward familiarity and novelty of stimuli [22], there is a paucity of studies using electroencephalography to examine this, particularly in the context of food choice behavior. Electroencephalography is a noninvasive technique used to measure brain activity in response to stimuli by recording event-related potentials (ERPs). So far, only a few studies have explored integrating electroencephalography, eye-tracking, and dot-probe methods to study attentional bias to food-related stimuli [23]. Of note, no previous study has taken stimulus novelty and familiarity into consideration, nor how the results of this integrated approach associate with the self-report food choices. Familiar stimuli evoke trust and perceived quality from previous positive experiences are suggested to influence an individual’s choices [24]. However, novel products require more cognitive effort to evaluate, leading to longer information processing times [25]. Thus, the main objective of this pilot study is to examine differences in attention to novel compared with familiar food stimuli, using 3 different attention indexes, including electroencephalography, eye tracking, and dot-probe. Indeed, it is hypothesized that participants will exhibit shorter reaction times (RTs) and longer total fixation durations (TFDs) for familiar compared to novel food items, indicating a stronger attentional bias toward familiar foods. In addition, familiar food items will elicit greater P300 amplitudes compared with novel food items, suggesting enhanced attentional engagement and processing.

## Methods

### Objectives

The secondary objectives of this study are to obtain preliminary data on the quality of the data, along with the potential correlations between visual attention metrics as assessed by eye tracking, RTs in response to the dot-probe task, and amplitude of ERP components. In addition, an exploratory objective of this study is to investigate the association between the data of attentional bias tools with the self-reported food choice to further our understanding of the potential of ERP and eye-tracking data in predicting the individual’s ultimate food choice, particularly taking stimulus familiarity into consideration.

### Study Design

This nonrandomized pilot study aims to use different measures of attention, via an integrated eye tracking and electroencephalography methodology, to study different aspects of the food-related attentional bias. Synchronization will ensure that eye movements and neural responses are recorded concurrently in response to the same stimuli during the dot-probe task, allowing precise alignment of data for accurate analysis.

### Study Setting

Data collection will be completed at the Iran University of Medical Sciences in Tehran, Iran, by trained research assistants and technicians.

#### Eligibility Criteria

The inclusion criteria include participants (1) aged between 18 and 50 years; (2) with a BMI within the healthy range (18.5-24.9 kg/m^2^), to avoid confounding effects of weight status on food preferences and attentional biases; (3) with normal or corrected-to-normal vision (required for accurate eye-tracking data and visual task completion; (4) who are right-handed, to control for hemispheric dominance effects in electroencephalography recordings, as handedness can influence attentional processing and ERP components (eg, P300, N100), reducing variability in neural responses; (5) with no history of neurological or psychiatric disorders, to minimize potential confounding factors that could influence the study outcomes; (6) with no use of medications affecting cognitive function or appetite including psychiatric medications, stimulants, or appetite suppressants; and (7) who are willing to complete the study tasks, including questionnaires, electroencephalography recordings, eye-tracking, and the dot-probe task.

The exclusion criteria include individuals with (1) a history of eating disorders or current disordered eating patterns; (2) a history of visual or motor impairments; (3) high sensitivity to visual stimuli, including photosensitivity, severe migraines, and epilepsy; or (4) an unwillingness to adhere to study protocol or incomplete or insufficient data collection during the study.

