### Sample Size

An a priori power analysis was conducted using G Power version 3.1.9.7 (Department of Psychology, Heinrich Heine University Düsseldorf) to determine the appropriate sample size needed to achieve sufficient statistical power for our study. The analysis was designed for an *F* test, with an assumed medium effect size of *F*=0.35, a significance level of α=.05, and a desired statistical power of 0.80. Based on these parameters, the calculated sample size required was 40 participants. Specifically, the number of groups (between-subject factor) was set at 2 (500 ms vs 2000 ms), and the number of measurements (within-subject factor) included 8 (2 stimulus types [familiar or novel] across 4 food categories). In addition, the correlation among repeated measures was conservatively set at 0.5. The medium effect size was chosen based on the existing literature on attentional bias studies, which commonly report medium to large effect sizes [23]. Under these specifications, G Power estimated an achieved power of 0.820, exceeding the commonly accepted threshold of 0.80 for adequate power. This indicates that a sample size of 40 participants is sufficient to detect a medium effect size in our primary outcome using repeated measures ANOVA, ensuring the study is powered to identify meaningful changes while balancing feasibility within the constraints of a pilot study.

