### Questionnaires

#### Demographic

The demographic questionnaire will be used to collect baseline information on participants to ensure that the study population is adequately characterized. The demographic questionnaire will collect information on age, gender, education level, socioeconomic status, smoking status, etc. The data gathered will be used for descriptive statistics, to stratify analyses, and to ensure that participants meet eligibility criteria.

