### Statistical Analysis

ERP data will be preprocessed with EEGLAB v14.1.2 toolbox for MATLAB [33], involving noise removal, epoching from stimulus onset to 1000 milliseconds post stimulus, and averaging across epochs to extract ERP components. Potentials reflecting ocular or muscle-related artifacts were removed using logistic infomax independent component analysis [34]. Further artifacts will be removed using the clean_rawdata plugin for EEGLAB.

Regarding dot-probe and electroencephalography attention-related measures (RTs, and N100 and P300 amplitudes, respectively), repeated measures ANOVA will be conducted, including the stimulus type (familiar vs novel across 4 food categories) as a within-subject factor, and group (500 ms vs 2000 ms) as a between-subject factor. Similarly, ANOVA will also be conducted to examine eye-tracking measures (TTFF, FD) between groups (500 ms vs 2000 ms). Post-hoc analyses will be conducted with Bonferroni adjustments for multiple comparisons. In addition, relationships between eye-tracking measures (TTFF, FD) and ERP components (P300 and N100 amplitudes) will be calculated by the Spearman correlation analysis. IBM SPSS Statistics 20 (IBM Corp) software will be used to analyze the data. No interim analyses are scheduled for this study.

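### The ANOVAs compare two nonrandomized presentation-time groups without adjusting for age, which spans 18 to 50 and is collected; this touches the group main effect only, and centred age should be a prespecified covariate

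*Protocol article*

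**What the plan says.** Eligibility Criteria admits participants "aged between 18 and 50 years". The same section restricts handedness to reduce variability in neural responses, and restricts BMI to avoid confounding.

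Study Design describes the work in these terms: "This nonrandomized pilot study aims to use different measures of attention". The article does not say how a participant comes to be in the 500 ms or the 2000 ms group.

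The Demographic section states: "The demographic questionnaire will collect information on age, gender, education level, socioeconomic status, smoking status, etc". On use, it says: "The data gathered will be used for descriptive statistics, to stratify analyses, and to ensure that participants meet eligibility criteria". No variable, cut-point or model is named for the stratification.

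Statistical Analysis specifies a repeated measures ANOVA for reaction time, N100 and P300. Familiar versus novel stimulus type, over the 4 food categories, varies within participants. Presentation time enters differently: "group (500 ms vs 2000 ms) as a between-subject factor". The eye-tracking measures (time to first fixation and fixation duration) get an ANOVA between the same two groups. No covariate appears in either model.

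Sample Size uses the same structure: "the number of groups (between-subject factor) was set at 2 (500 ms vs 2000 ms", with 8 measurements, a correlation of 0.5, f = 0.35 and alpha 0.05. It reports N = 40 and power 0.820.

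**The concern.** A comparison of two separate groups of people carries all between-person variation in its error term. Part of that variation may be explained by age, which has a 32-year range here and is already recorded. Leaving age out of the model gives away whatever precision it would buy.

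The groups are also not randomized, so the design does nothing to keep them alike in age. If one group is systematically older, the age effect is counted as an effect of presentation time.

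Both problems fall on the group main effect and on the between-group eye-tracking ANOVA. Statistical Analysis writes the model out and the Demographic section states what the demographic data are for, so this is a choice the article has made, not only a detail left to a fuller plan.

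**Working it through.** **Inputs from Sample Size.** N = 40, f = 0.35, m = 8 measurements, rho = 0.5, 2 groups, alpha = 0.05.

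**1. Which test gives the stated power?**

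- Between-group test: lambda = f² × N × m / (1 + (m − 1) × rho) = 0.1225 × 40 × 8 / 4.5 = 8.71. With F(1, 38), power is 0.8202, which matches the stated 0.820. N = 38 gives 0.799, so 40 is the smallest even N that reaches 0.80.
- Within-subject or interaction test: lambda = f² × N × m / (1 − rho) = 0.1225 × 40 × 8 / 0.5 = 78.4. With F(7, 266), power exceeds 0.999.

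So N = 40 rests on the group main effect, the test that age can affect.

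**2. Which effects does age touch?** Suppose age adds the same amount to every one of a participant's 8 measurements.

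- Familiar minus novel, within a participant: the age term subtracts out.
- That difference compared between 500 ms and 2000 ms (the interaction): the age term is already gone.
- The participant's mean compared between groups: the age term remains, in the error and, if mean ages differ, in the estimate.

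**3. Gain from adjustment.** Let r be the correlation of age with a participant's mean outcome within groups. The article gives no value, so 0.2 to 0.5 is assumed. With age in the model and the groups balanced on age, lambda becomes 8.71 / (1 − r²), tested on F(1, 37). The last column is 40 / (1 − r²), the unadjusted sample size with the same lambda.

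| r | 1 − r² | lambda | power | equivalent N |
|---|---|---|---|---|
| 0 | 1.00 | 8.71 | 0.820 | 40 |
| 0.2 | 0.96 | 9.07 | 0.835 | 42 |
| 0.3 | 0.91 | 9.57 | 0.854 | 44 |
| 0.4 | 0.84 | 10.37 | 0.880 | 48 |
| 0.5 | 0.75 | 11.61 | 0.913 | 53 |

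The r = 0 row is the full price of the fix: power goes from 0.8202 to 0.8197.

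**4. Bias from a systematic age gap.** In SD units of the participant mean, bias = r × (age gap / SD of age). The article gives neither r nor the gap. As an illustration only, a gap of half an age SD with r of 0.2 to 0.5 shifts the group contrast by 0.10 to 0.25 SD. The planned effect on the same scale is 2 × 0.35 / sqrt(4.5/8) = 0.70 / 0.75 = 0.93 SD.

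**The case against.** The strongest reply is that the affected test is not the study question. The stated hypotheses on reaction time, total fixation duration and P300 all compare familiar with novel items within a participant, and the primary outcome asks about that bias at different presentation times. Age, if additive, drops out of both. This stands, and it limits the point to the group main effect and the between-group eye-tracking ANOVA. Those tests are nevertheless specified, and one of them sets the sample size.

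The second reply concerns the design. The Dot-Probe Task section shows each pair for either 500 or 2000 ms within one 128-trial experiment, each pair appearing 8 times. Eight equals 2 sides × 2 probe positions × 2 durations, which would fit both durations being shown to everyone, though the article does not say so. On that reading there are no groups to differ in age, and adjustment brings no gain. Sample Size and Statistical Analysis both declare duration between-subject, so the point holds on the stated model but is conditional on it.

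Third, covariates are often left to a fuller plan, and the Demographic section does mention stratified analyses. That mention is too unspecific to count as adjustment of the stated model. It is not itself an error either.

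Three stronger readings are tempting and are not supported:

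- **That the power of 0.820 is wrong.** It reproduces exactly; adjustment only adds to it.
- **That chance imbalance in age is an uncorrected bias.** If ages were uniform over 18 to 50, the SD would be 32/√12 = 9.24 years. The 95% limit for the gap between two randomized groups of 20 would then be 1.96 × 9.24 × √(2/20) = 5.7 years. A gap of that kind is already allowed for in the unadjusted test's error term and 5% level. Only a systematic difference biases the comparison, and the article does not show that one exists.
- **That stratification would cut the groups into unworkably small cells and must be dropped.** The article defines no such cells.

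**Conclusion.** The point holds in a limited form. As written, the models leave age out of a nonrandomized between-group comparison although age is available, and the comparison concerned is the one behind N = 40. The likely benefit of adjusting is modest: power of about 0.83 to 0.91 instead of 0.82 for an assumed correlation of 0.2 to 0.5, and no material loss if age is unrelated to the outcome. Adjustment also removes bias from a systematic age difference between the groups, to the extent that the age effect is linear as modelled. The size of that bias cannot be stated from the article.

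The conclusion rests on duration being between-subject, as Sample Size and Statistical Analysis say, and on an additive age effect. It casts no doubt on the familiar-versus-novel contrast or on its interaction with duration.

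**What to change.** 1. In Statistical Analysis, add age, centred at the sample mean, as a prespecified continuous covariate in the repeated measures ANOVAs for reaction time, N100 and P300 and in the between-group ANOVA for the eye-tracking measures. Centring is needed because an uncentred covariate in the SPSS repeated measures procedure changes the test of the within-subject familiarity factor.
2. Reconcile the Dot-Probe Task section with Sample Size and Statistical Analysis on whether each participant sees one duration or both. If one, say how participants are assigned to it. If both, the age covariate brings no gain and can be left out.

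The demographic stratification can stay. The cost is one line in the plan and one error degree of freedom in the group test, with no new data. The article states that data analysis had not begun at submission, so on that statement the change could still be prespecified.

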Integrating these perspectives, our study seeks to build upon these observations by investigating how familiarity and novelty interact with attentional biases, potentially offering a new understanding of how these factors shape food choices. A recent study investigating electroencephalography measures of attention toward food-related stimuli in neophobic individuals proposed that food neophobia might be associated with attentional biases toward novel foods. However, the results indicated that implicit behavioral and attentional processing were affected across all food types, regardless of familiarity [40]. This finding, alongside several other studies [23,41] examining attentional differences toward food stimuli based on factors such as calorie content and familiarity across diverse populations, underscores the importance of using multiple methods to capture different dimensions of attention. This study serves as an initial step in piloting an integrated approach, combining electroencephalography, eye tracking, and a dot-probe task, to gather preliminary data on the feasibility of using this multimodal framework to assess attentional responses to familiar versus unfamiliar food stimuli in healthy adults. A recent systematic review and meta-analysis on attentional bias toward food in individuals with overweight and obesity [42] highlighted the poor reliability of eye tracking and the dot-probe task, 2 commonly used methods for measuring attentional bias. The review emphasized that the poor psychometric properties of these measures represent a significant limitation in attentional bias research. In light of this, the present study’s integration of 3 different attentional bias tools is a key strength, offering a more comprehensive approach to capturing multiple dimensions of attentional processes. In addition, this study has several other strengths. First, the integration of eye-tracking, electroencephalography, and the dot-probe task is a novel approach that allows for a comprehensive analysis of attentional biases towards food stimuli. Second, by examining attentional biases toward familiar or novel food stimuli, the study addresses an important aspect of consumer behavior with implications for both health behaviors and marketing strategies. Third, the use of multiple measures (eg, TTFF, TFD, RTs, P300, N100) enhances the reliability of the findings and provides a solid foundation for validating results in future studies.

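### A data-quality outcome is written as a person-level eligibility exclusion, which conflicts with the objective of learning about data quality

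*Protocol article*

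**What the plan says.** In Eligibility Criteria, the fourth exclusion in the Protocol article covers people who will not follow the protocol and, in the same item, "incomplete or insufficient data collection during the study". The unit excluded is the person. The text gives no threshold for insufficient data and does not say which of the three recordings it refers to.

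Three other places bear on this:

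- **Objectives:** "The secondary objectives of this study are to obtain preliminary data on the quality of the data", followed by the correlations between the measures.
- **Discussion, Principal Findings:** the study is a first step "to gather preliminary data on the feasibility of using this multimodal framework". The limitations paragraph there accepts that recording EEG and gaze together can cause technical problems and artifacts.
- **Abstract (Methods) and Sample Size:** "A total of 40 healthy adult participants will be recruited", and 40 is also the required number from the power analysis, where "G Power estimated an achieved power of 0.820". The article states neither a loss allowance nor a replacement rule.

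**The concern.** An eligibility criterion should be decidable before a person enters the study. This one depends on what happens during the recording session. It therefore selects participants on an outcome, and that outcome is the one the data-quality objective is about. The people in whom combined recording fails are the most informative for that objective, and they are the people the criterion removes.

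The clause also works on whole persons although three separate measures are taken. If it is applied to the person whenever any one recording is inadequate, a failed EEG would also take out valid reaction times and gaze data. The comparisons would then use only people complete on everything.

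Finally, if exclusions come out of the 40 recruited, the analysed number is below the 40 for which power was stated.

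**Working it through.** **1. The passages side by side.** The other exclusions (eating disorder history, visual or motor impairment, sensitivity to visual stimuli) can be established at screening. Incomplete or insufficient data cannot. The Objectives ask how good the data are, whereas the criterion keeps only people whose data were good enough. Both cannot be followed literally without biasing the answer to the first.

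**2. Illustration of the selection (assumed rate).** Suppose 34 of 40 tested people give usable recordings on all modalities: 34/40 = 85%. If the other 6 are treated as ineligible and also left uncounted, the retained sample shows 34/34 = 100%. If they are counted, 85% is recovered. The size of the distortion depends on that reporting choice, which the article does not state.

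**3. Reproducing the stated power.** Inputs from Sample Size: f = 0.35, α = 0.05, k = 2 groups, m = 8 measurements, ρ = 0.5, N = 40.

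Between-factor test of a repeated measures ANOVA: λ = f²·N·m / [1 + (m − 1)ρ], with df₁ = k − 1 and df₂ = N − k.

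λ = 0.1225 × 40 × 8 / (1 + 7 × 0.5) = 39.2 / 4.5 = 8.711, with df 1 and 38. Power = 0.8202, which matches the stated 0.820. The stated figure is therefore for the 500 ms versus 2000 ms comparison.

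**4. The same test with fewer analysable people (assumed losses).**

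| Analysed N | Loss from 40 | λ | Power |
|---|---|---|---|
| 40 | 0 | 8.711 | 0.820 |
| 39 | 1 | 8.493 | 0.810 |
| 38 | 2 (5%) | 8.276 | 0.799 |
| 36 | 4 (10%) | 7.840 | 0.776 |
| 34 | 6 (15%) | 7.404 | 0.751 |
| 30 | 10 (25%) | 6.533 | 0.694 |

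One loss keeps power above 0.80; two bring it marginally below.

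**5. The within-subject test.** λ = f²·N·m / (1 − ρ), with df₁ = m − 1 and df₂ = (N − k)(m − 1), no sphericity correction. At N = 40, λ = 39.2 / 0.5 = 78.4; at N = 30, λ = 29.4 / 0.5 = 58.8. Power exceeds 0.999 at both. The group-by-measurement interaction gives the same values, because with two groups its degrees of freedom are the same.

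**6. Recruitment needed to keep 40 analysable.** N / (1 − d), rounded up: 40/0.95 gives 43, 40/0.90 gives 45, 40/0.85 gives 48. These loss rates are assumptions too.

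**The case against.** The strongest reply is that this is only a matter of wording and placement. The article defines no participant-level success rate, and its listed secondary outcomes are correlations. Data quality could mean signal- or trial-level quality (accuracy, reaction-time outliers, calibration, impedance, artifacts), which can be measured in those retained. The data-handling rules that are given work on trials or segments, not on persons. Analysis sets and replacement rules commonly sit in a full protocol or SAP, and recruiting 40 could mean recruiting until 40 are usable.

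Much of this stands, and it rules out several stronger readings:

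- **That usability will come out near 100% by construction.** This follows only if excluded people are also left uncounted, and the article does not say so.
- **That valid reaction times and gaze data will be discarded when only the EEG fails.** This is one reading of a clause that names no modality.
- **That the pilot cannot inform a larger study.** Effect estimates, variances and correlations would still do so.
- **That the familiar-versus-novel hypotheses lose power.** Under the protocol's own inputs the within-subject test is not materially affected.

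The core remains. Signal quality measured only in retained people is still measured in a sample selected on it. An unseen SAP can define analysis sets, but it does not correct an eligibility criterion that already removes these participants. This is stated text that is badly fixed, not a missing detail.

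**Conclusion.** The point holds: a result of testing is written as a person-level entry exclusion, without a threshold, and it conflicts with the data-quality objective and the feasibility purpose. The conclusion comes from the text and needs no assumed loss rate. How far data quality would be overstated cannot be given, because the article supplies no loss rate and does not say whether excluded people are counted.

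The power point is secondary. It assumes that losses come out of the 40 and are not replaced. Power for the 500 versus 2000 ms comparison then goes from 0.820 to 0.799 with two losses, which is immaterial in itself, and to 0.751 with six. A reader should not infer that the familiarity comparison is underpowered for this reason.

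**What to change.** Take the data-sufficiency clause out of the exclusion criteria and restate it as an analysis-set rule for each modality, with a stated threshold, so that a failed recording affects only the analyses that need it. The clause should be moved, not just deleted; otherwise the article has no participant-level rule for unusable recordings. Keep every tested participant as the denominator for data quality, and report usable-data rates for EEG, eye tracking and dot-probe separately and jointly.

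In Sample Size, state that 0.820 refers to 40 analysable participants and to the between-group test, and give the values for 38, 36 and 34 beside it, marked as assumed losses. If excluded people are to be replaced, say so.

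The cost is an edit to one criterion, a sentence or two in Sample Size and a flow count by modality. The article reports that analysis had not begun, so the rule can still be fixed before results are seen. The downside is that the number analysed will differ between metrics and must be shown with each result.
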